### Study design

This study is funded by the National Major Science and Technology Project of China on the prevention and treatment of infectious diseases, for human immunodeficiency virus and HBV [2008ZX10002-026]. This clinical trial is a registered [NCT00725335], prospective, intraoperatively randomized multicenter trial of patients undergoing curative resection for HCC. The patients will be stratified by center and allocated to groups by a permuted-blocks randomization protocol. The primary objective of this study is to compare the disease free-survival rates at 1, 2, and 3 years postoperatively between the two groups. We hypothesize that the long-term prognosis of patients who have undergone curative resection will be worse in the control group (Pringle maneuver) than in the experimental group (non-Pringle maneuver).

The detailed study design is shown in Figure1.

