## Methods

### Aims of the study

This trial aims to assess the long-term effects of the Pringle maneuver on the rate of tumor recurrence after curative resection of HCC. The effects on disease-free survival, overall survival, operative morbidity and mortality, duration of operation, blood loss, transfusion requirements, hospital stay, intensive care unit stay, and blood test results with prognostic relevance, will be examined. The trial will test whether hepatic resection without the Pringle maneuver reduces recurrence rate and improves disease-free survival rate.

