### Sample size calculation and data analysis plan

The sample size of this trial was calculated using data from our previous experience and from the published literature. There are currently no data from randomized controlled trials showing the recurrence rate of HCC after hepatectomy without the Pringle maneuver. Most studies used the Pringle maneuver. This trial plans to have equal numbers of control and experimental subjects, and a 36-month follow-up period. The median survival time after the treatment that the control group will receive has been reported to be 26 months [24,44-50]. We anticipate a10-month difference in the median recurrence-free survival time between the experimental and control groups. If median survival times in the control and experimental groups are 26 months and 36 months, respectively, we will need to include 249 experimental subjects and 249 control subjects to be able to reject the null hypothesis that the experimental and control survival curves are equal with a probability (power) of 0.800. The Type I error probability associated with this test of the null hypothesis is 0.05.

Data for primary and secondary outcome measures will be analyzed using the SPSS statistical software package (SPSS UK Ltd., Woking, U.K.). Analysis will include standard descriptive statistics, Student’s t tests, correlation and regression, and two-way (group x time) repeated measures ANOVA to examine differences between the groups over time. Survival analysis will be performed. Statistical significance will be set at p < 0.05and all tests will be two-tailed. Subgroup stratified analysis will be performed according to tumor size, tumor encapsulation, Edmondson’s grade, HBV load, ischemic time, blood loss, and transfusion. The intention-to-treat analysis will be used for the patients whose portal triad clamping was changed due to safety reasons.

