### Endpoints

The primary trial endpoint will be tumor recurrence diagnosed by enhanced CT scan or serum alpha-fetoprotein level. Secondary objectives are to examine overall survival, blood loss, duration of operation, requirement for blood transfusion, length of hospital stay, and morbidity rate. The formal end of the study will be at the end of the 3-year follow-up period of the last patient to be enrolled. All these parameters will be recorded prospectively as part of the study protocol. Final evaluation of the primary and secondary endpoints of the study will be performed 1 year after enrollment of the last patient.

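### The primary endpoint is named differently in four sections; none says whether death without recurrence counts or which comparison decides the trial

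*Protocol article*

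**What the plan says.** Four sections of the protocol article bear on the primary endpoint.

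- **Aims of the study** starts from the effect on the rate of recurrence and lists disease-free survival among further effects to be examined. It then puts the two side by side: "The trial will test whether hepatic resection without the Pringle maneuver reduces recurrence rate and improves disease-free survival rate".
- **Study design** gives the primary objective as to "compare the disease free-survival rates at 1, 2, and 3 years postoperatively between the two groups".
- **Endpoints** states: "The primary trial endpoint will be tumor recurrence diagnosed by enhanced CT scan or serum alpha-fetoprotein level". It mentions neither death nor a time point. Overall survival is secondary; disease-free survival is in neither list.
- **Sample size calculation and data analysis plan** anticipates ten months' "difference in the median recurrence-free survival time between the experimental and control groups". It sizes the trial to "reject the null hypothesis that the experimental and control survival curves are equal with a probability (power) of 0.800", with medians of 26 and 36 months, and adds: "The Type I error probability associated with this test of the null hypothesis is 0.05". The same section sets a two-tailed 0.05 level for all tests and refers to survival analysis only in general terms.

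**The concern.** Two things are left open.

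**The event.** Recurrence alone and disease-free or recurrence-free survival usually part company over a patient who dies without recurrence. The article defines none of the three terms in this respect. If such deaths differ between the arms, a recurrence endpoint that censors or ignores them and a survival endpoint that counts them can lead to different conclusions. Background gives reasons why a difference is conceivable in either direction: clamping reduces blood loss but injures the liver remnant. It gives no death rate.

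**The comparison.** Rates at three fixed times, an undated recurrence endpoint and a whole-curve test are different analyses with different power. If the text does not say which one decides the trial, the choice can be made after the data are seen.

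**Working it through.** **Inputs** (Sample size section unless noted): medians 26 and 36 months; 249 per arm; power 0.80; two-sided 0.05; 36 months' follow-up; 9 months' recruitment (Duration of the trial). Assumed here: exponential survival, uniform accrual, no dropout.

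**1. Reproducing 249 per arm.** Hazard ratio = 26/36 = 0.722, ln = −0.3254.

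- Events (Schoenfeld) = 4 × (1.960 + 0.842)² / 0.3254² = 296.5, rounded up to 297. Freedman's formula gives 302.
- Event probability with accrual A = 9, follow-up F = 36 and λ = ln 2/median: 1 − [exp(−λF) − exp(−λ(A+F))]/(λA) = 0.659 (control) and 0.541 (experimental), mean 0.600.
- n per arm = 297/0.600/2 = 247.4 (Schoenfeld) or 251.6 (Freedman). The stated 249 is reproduced.
- At 498 patients: 298.9 events; power = Φ(0.3254 × √298.9/2 − 1.960) = Φ(0.853) = 0.803.

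So 249 per arm fits one two-sided log-rank test with follow-up running until the last patient reaches 36 months. If every patient is cut at exactly 36 months, the event probabilities are 0.617 and 0.500. That gives 278.1 events and power Φ(0.753) = 0.774, and 266 to 270 per arm would be needed for 0.80.

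**2. The fixed-time reading.** S(t) = 0.5^(t/median). Power = Φ[(d − 1.960·se₀)/se₁], where d is the difference in rates, se₀ the pooled and se₁ the unpooled standard error with 249 per arm, and follow-up is complete.

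| Time | Control | Experimental | d | se₀ | se₁ | Power at 0.05 | n per arm for 0.80 | Power at 0.0167 |
|---|---|---|---|---|---|---|---|---|
| 1 year | 0.726 | 0.794 | 0.067 | 0.0383 | 0.0382 | 0.42 | 628 | 0.26 |
| 2 years | 0.527 | 0.630 | 0.103 | 0.0443 | 0.0440 | 0.64 | 363 | 0.47 |
| 3 years | 0.383 | 0.500 | 0.117 | 0.0445 | 0.0442 | 0.75 | 282 | 0.59 |

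The last column applies a Bonferroni level of 0.05/3.

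**3. Familywise error if the three times are three tests at 0.05.** For independent tests: 1 − 0.95³ = 0.143. The estimates are correlated, with ρ(s,t) = √[v(s)/v(t)] for s < t and v = (1 − S)/S. A common median of 26 months gives 0.65 (years 1 and 2), 0.48 (1 and 3) and 0.75 (2 and 3). A common median of 36 months gives 0.67, 0.51 and 0.77. Two million multivariate normal draws for each give 0.114 and 0.112, so about 11%.

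**4. Death without recurrence.** No calculation is possible. The documents give neither the rate of such deaths nor a difference between arms.

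**The case against.** The strongest defence is that the sections can be read as one coherent plan. Disease-free and recurrence-free survival are often synonyms, so Study design and the Sample size section may describe one endpoint. Study design states an objective and names no test. The Sample size section names one null hypothesis and one error rate, so the yearly rates may only describe a single curve. Handling of multiplicity may also sit in an analysis plan that is not shown.

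Much of this stands. A reader might infer that the protocol commits itself to three uncorrected primary tests; the text does not say so, and the 11% and the fixed-time powers apply only on that reading. A reader might also infer that the Endpoints section excludes deaths and that Study design counts them; neither section defines its event. Nor do the documents show more non-recurrence deaths without clamping. They support more blood loss, allow clamping for safety in the non-Pringle arm, and restrict entry to Child-Pugh A.

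The defence does not remove the conflict over what is primary. Recurrence in Endpoints and disease-free survival in Study design remain two answers to the same question, and Aims of the study names both. An unseen analysis plan could choose between them but would not make these sections agree.

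**Conclusion.** The point holds as an inconsistency in the protocol's own text: the primary endpoint is recurrence in one section, disease-free survival rates at three times in another, both in a third, and a whole recurrence-free survival curve for sizing. The handling of death without recurrence and the deciding comparison are not stated. How far this could shift the result is unknown, since it depends on non-recurrence deaths differing by arm.

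Conditionally on three separate tests at 0.05, the familywise error is about 11% rather than 5%, and no single time point reaches 0.80. These figures rest on exponential survival and no dropout.

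It would be wrong to infer that the sample size is miscalculated. The 249 per arm reproduces, but for one log-rank test over the curves, which no section names as the primary analysis.

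**What to change.** In Aims of the study, Study design, Sample size calculation and Endpoints, name one primary endpoint: time from randomisation to first recurrence or death from any cause. Test it once, with a log-rank test stratified by centre to match the randomisation, at two-sided 0.05.

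Use all follow-up until the last patient reaches 36 months (about 299 events, power about 0.80). If every patient is to be cut at 36 months, restate the power as about 0.77. Either version requires analysis at the end of the three-year follow-up, so the sentence in Endpoints that places final evaluation one year after the last enrolment must be reconciled with it.

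Report the 1-, 2- and 3-year Kaplan-Meier rates with confidence intervals as description, and time to recurrence, with death as a competing event, as secondary.

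The cost is a change of wording. No new data are needed, because deaths are already recorded for overall survival, and the sample size stays at 498. The small price is that recurrence alone is no longer the primary endpoint.

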**Figure 1 F1:**
[figure not shown]
**Detailed flow chart of the clinical trial.** Eligible patients from five centers will be enrolled, and randomly divided into an experimental group and a control group by permuted-blocks randomization. Each patient will be followed up for 3 years after their primary operation.

### Surgical interventions

All surgical interventions in this trial are described in the study protocol.

### Incision lines and decision-making

Specific teams of surgeons have been designated in each center participating in this trial, and have completed the operative and postoperative management training for following the protocol. The abdominal incision can be decided according to the surgeon’s preference. A complete exploration of the abdomen and an intraoperative ultrasound evaluation of the whole liver will be performed to decide whether curative resection is feasible. If necessary, frozen section biopsies will be taken to evaluate suspicious lesions or lymph nodes. If both intervention procedures seem possible to the surgeon, randomization will be performed at this time point.

### Experimental group (group a, non-Pringle group)

The liver will be mobilized from the retroperitoneum and the peripheral ligament. Anatomical liver resection is preferable. If anatomical resection is not possible, a surgical margin of more than 2 cm should be achieved, except if the location of tumor nodes makes this impossible (e.g., close to the inferior vena cava or portal vein).The resection method and surgical margin will be recorded for analysis. The liver parenchyma can be resected according to the surgeon’s preference and local standards (CUSA, Tissue-link.). The Pringle maneuver will not be used, and hepatic inflow and outflow will be maintained. For safety, the surgeon may use the Pringle maneuver if major bleeding occurs.

### Control group (group B, Pringle maneuver group)

After mobilization, the Pringle maneuver will be performed. The same approach will be used for hepatic parenchymal transection as in the experimental group. If necessary, the outflow of the hepatic vein can be controlled, and this factor will be analyzed. For safety, the surgeon may change the surgical technique at any time during the operation.

### Pringle maneuver

The portal triad clamping is set to 15 min hepatic inflow occlusion followed by 5 min of reperfusion, repeated as needed. The last occlusion should be 15 min even if the transection has been completed. The total ischemia and reperfusion times and the number of occlusion cycles will be recorded for analysis. Any deviation in the standard operating procedures will be regarded as a protocol violation.

### Surgical team

The surgical teams consist of senior surgeons who all have standard qualifications and have independently performed standard anatomical hepatectomy in more than 100 patients. The results of randomization will be made known to the operating surgeon only after the disease has been deemed suitable for curative resection. All surgical procedures and anesthesia will be performed by the specifically trained teams of experienced hepatobiliary surgeons and anesthesiologists, ensuring standardized execution of the study protocol. Patients will be randomly assigned to eligible surgeons to minimize the effects of variations between surgeons on operative outcomes.

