### Randomization, stratification, and blinding

This is a randomized multicenter study. After giving informed consent and being enrolled in the study, patients will be randomized into different groups in the operating room after surgical exploration. The permuted-blocks randomization protocol will comprise five separate randomization lists, one for each participating hospital, and will be centrally managed by the Clinical Trial Center of the lead hospital, the Third Military Medical University. When an eligible case is enrolled, the Clinical Trial Center will be called and a randomization number will be assigned according to the designated list. Because there are two groups in this trial, the block sizes will be 4, 6, and 8 and will be randomly assigned. Patients will be stratified by site and randomized in a ratio of 1:1 into the two groups. Patients and outcome assessors will be blinded to achieve a minimum bias.

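### The plan expects random assignment to surgeons to deal with surgeon variation, but the t tests it names for operative outcomes leave surgeon and centre variance in the error: valid, but less precise than it need be

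*Protocol article*

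**What the plan says.** Three statements bear on this point, all in the Methods of the protocol article.

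- Surgical team: "Patients will be randomly assigned to eligible surgeons to minimize the effects of variations between surgeons on operative outcomes". The number of surgeons is not given.
- Randomization, stratification, and blinding: technique is allocated from "five separate randomization lists, one for each participating hospital". The only stratum is the site ("Patients will be stratified by site and randomized in a ratio of 1:1 into the two groups"), and on blocking it says "the block sizes will be 4, 6, and 8 and will be randomly assigned". Surgeon is not a stratum.
- Sample size calculation and data analysis plan: "Analysis will include standard descriptive statistics, Student’s t tests, correlation and regression, and two-way (group x time) repeated measures ANOVA". It adds "Survival analysis will be performed" and "all tests will be two-tailed". No surgeon or centre term is named, surgeon is not among the listed subgroup factors, and outcomes are not matched to tests.

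Under Endpoints, blood loss, duration of operation, transfusion, hospital stay and morbidity are secondary. Recurrence is primary.

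**The concern.** The article treats the surgeon as a source of variation in operative outcomes and names a mechanism meant to deal with it. That mechanism does only part of the job. Random assignment of patients stops one surgeon from receiving systematically harder cases. Surgeons still differ in usual blood loss or operating time, and a given surgeon's patients need not split evenly between techniques, because the technique lists run by hospital.

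What remains can be recovered only in the analysis. A plain two-sample t test pools all patients in an arm, so differences between surgeons and between centres count as noise. The operative outcomes are the short-term price of not clamping, so the width of their intervals matters to a reader weighing the two techniques. The trial already assigns the surgeon as a design factor, so leaving it unused wastes information the trial has paid for.

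**Working it through.** **1. The plan's own figure.** With medians of 26 and 36 months, the hazard ratio is 26/36 = 0.722 under exponential survival. Events needed (Schoenfeld) = 4 × (1.96 + 0.8416)² / (ln 0.722)² = 296.5, so 297. With 9 months of uniform accrual and 36 further months of follow-up, the event probability is 0.659 (control) and 0.541 (experimental), mean 0.600. Then 297 / 0.600 / 2 gives 248 per arm. Using the average median of 31 months, the event probability is 0.595 and 296.5 / 0.595 / 2 = 249.1. The stated 249 per arm is reproduced, and nothing below changes it.

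**2. Inputs for the surgeon question.** From the article: N = 498, 1:1 allocation, five hospital lists. Assumed, because the article does not give them: S = 20 surgeons (about 25 patients each) and a surgeon ICC of 0 to 0.20. Outcomes are scaled to total variance 1.

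**3. Standard error (SE) of the arm difference.**

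- t test: SE = √[4(1 − ICC/S)/N]. The small ICC/S term arises because the sample contains only S surgeons.
- With surgeon intercepts: SE = √[4(1 − ICC)/(N − (S − 5))]. The S − 5 is the information lost to uneven splits within surgeons, given that the lists already balance the five hospitals.

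| ICC | t test | with surgeon | change in SE |
|---|---|---|---|
| 0 | 0.0896 | 0.0910 | +1.5% |
| 0.05 | 0.0895 | 0.0887 | −0.9% |
| 0.10 | 0.0894 | 0.0863 | −3.4% |
| 0.20 | 0.0892 | 0.0814 | −8.7% |

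In terms of patients, (0.0894/0.0863)² = 1.07 and (0.0892/0.0814)² = 1.20. The narrower interval is what about 7% or 20% more patients would give.

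**4. Check by simulation.** 1,500 runs per setting used hospital-level permuted blocks of 4, 6 and 8 and random assignment to surgeons within hospital. Mean SEs (t test, then with surgeon) agree with the formulas:

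| S | ICC 0.10 | ICC 0.20 |
|---|---|---|
| 10 | 0.0892, 0.0855 | 0.0885, 0.0804 |
| 15 | 0.0893, 0.0859 | 0.0887, 0.0809 |
| 25 | 0.0893, 0.0868 | 0.0894, 0.0819 |

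The reduction is 3 to 4% at ICC 0.10 and 8 to 9% at 0.20.

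**5. Validity of the t test.** When surgeons differ only in level, the simulated type I error of the t test was 0.035 to 0.057 over all settings. The Monte Carlo standard error at 0.05 is √(0.05 × 0.95/1500) = 0.006. There is no sign of inflation.

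**6. If the technique effect itself differs between surgeons.** With variance τ² of surgeon-specific technique effects and inference to surgeons in general, Var = 4/N + τ²/S. At S = 20, τ = 0.2 gives 0.00803 + 0.00200 and an SE ratio of 1.12. At τ = 0.3 it is 0.00803 + 0.00450 and a ratio of 1.25. At τ = 0 the ratio is 1. No value of τ can be taken from the article.

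**The case against.** The strongest reply is that this is a condensed article. Model covariates are commonly left to an analysis plan, and the methods listed include regression, under which a surgeon term could fit. That stands, so the mere absence of a surgeon term is not an error. What remains is narrower: the article says that surgeon variation is dealt with, gives a mechanism that does so only in part, and names a test that does not do the rest.

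It can also be said that technique is drawn in the operating room after exploration, so the surgeon is settled before allocation and is independent of arm. Stratifying by site alone is legitimate, and uneven splits within a surgeon are chance, not bias. All of this stands, and it is why the t test remains valid.

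A reader might go further and infer that all outcomes go to plain t tests and that the intervals are too narrow. The article supports neither. It also lists "standard descriptive statistics, Student’s t tests, correlation and regression", repeated measures ANOVA and survival analysis, and a time-to-recurrence endpoint would not go to a t test. Intervals that are too narrow require both a technique effect that varies between surgeons and a target of surgeons beyond those in the trial. The surgeon's freedom over transection method and over changing the clamping makes such variation plausible, and the Discussion looks to wider practice. But the article gives no size for the variation and does not state that target for the operative comparisons. For the trial's own surgeons the t-test interval is not too narrow.

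**Conclusion.** The concern holds as a minor point about precision. Random assignment to surgeons evens case mix only, and a t test leaves surgeon and centre variance in the error for blood loss, duration of operation and hospital stay. On the assumption of 20 surgeons, a surgeon term would reduce the standard error by about 3% at an ICC of 0.10 and 9% at 0.20, do almost nothing at 0.05, and cost about 1.5% at zero. These percentages are for continuous outcomes and rest on assumed values, since the article gives neither the number of surgeons nor the ICC.

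The t test keeps its type I error when surgeons differ only in level. Any inflation from surgeon-specific technique effects is conditional on heterogeneity that the article does not quantify, and is not a finding here. The 498 patients and the primary time-to-recurrence analysis are not affected.

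**What to change.** In the data analysis section, state that operative outcomes are compared with a regression or mixed model: group as fixed effect, surgeon within centre as random intercept. Use the logistic form for morbidity and for transfusion yes/no. Define surgeon as the one to whom the patient was assigned, so that the factor is fixed before technique is drawn. In the Surgical team section, say that random assignment balances case mix between surgeons and that the analysis accounts for surgeon differences.

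Variation of the technique effect between surgeons may be explored as a sensitivity analysis only. A random slope in the main model is a debatable trade: under the scenarios in step 6 it widens the standard error by about 12% to 25%, and a surgeon intercept alone does not address that variation.

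The cost is a change of wording and the identity of the assigned surgeon in the data set. The downside is a few degrees of freedom, some surgeons with few cases, and a slight loss of precision if surgeons do not differ. No patients or visits are added.
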